#### Clinic survey

The clinic manager/lead clinician will complete a Clinic Survey capturing structural (type, size, number of FTE clinicians, patient panel demographics, payer sources), operational (use of QI strategies such as team huddles and audit & feedback), and EHR characteristics. We will use REDCap to create the survey, and field data collectors will distribute QR codes to all clinic members to complete it anonymously.

#### Clinic member survey

The Clinic Member Survey will include adapted SPARCCS survey items (for clinicians) and clinic readiness, capacity to implement change, leadership, implementation climate and culture, teamwork, and team communication (for all clinic members)—attributes associated with implementation success [41, 42, 104–109].

#### Cost surveys

Measure cost to clinics of implementing the intervention. Clinic managers will complete a survey once every year during the intervention providing personnel time, salary information, cost of materials, and medical care costs related to intervention start-up: (1) personnel effort, software, hardware and costs related to workflow modification, (2) time and effort assigning coordinator responsibilities and identifying eligible patients, (3) tele-mentoring delivery and participation, and intervention execution costs including: (1) effort of staff assigned to care coordinator role, workflow modification(s), cancer documentation, EHR tool maintenance as applicable, and (2) healthcare utilization costs for survivors receiving the intervention.

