### Implementation strategies

Two strategies (partner engagement and practice facilitation) will support intervention. Our evaluation will identify other emergent strategies and delineate mechanisms of implementation (Aim 3).

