
#### Practice facilitation

We will support each clinic’s intervention implementation by providing facilitation in quality improvement (QI) by a trained facilitator [78]. Facilitators will employ strategies to promote QI activities while also building capacity, [79] while strengthening our relationship with each CHC and team. Strategies include building relationships within teams, providing value by contributing EHR expertise, and remaining flexible throughout the QI change effort [80]. Facilitators will determine each clinic team’s readiness for change using the Organizational Readiness for Change measure [81] and will identify current needs and “pain points” [82]. While we have clinic leadership buy-in, it is critical to also cultivate buy-in from team members on the ground to promote intervention adoption. The facilitator will work with clinic teams in designing intervention forms that will achieve the tracking and coordinating functions. For example, the facilitator will support the designated care coordinator in planning and testing the process of assessing and monitoring survivors’ survivorship care needs. They will utilize established techniques such as PDSA cycles [83], clarifying roles and identifying champions [50], building trust through experience-based problem solving [84], workflow modification via cognitive walk-throughs [85, 86].

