#### Cost and cost-effectiveness analyses

We will estimate the incremental cost effectiveness ratio (ICER) [124, 125], which is the incremental cost of the intervention compared to usual care divided by the incremental difference in the proportion of patients receiving guideline appropriate care. The 95% confidence interval for the ICER assesses uncertainty through a nonparametric bootstrapping approach [126]. If the ICER replicates cover more than one quadrant of the cost-effectiveness plane, the cost-effectiveness acceptability curve approach will be used to capture the uncertainty [127–129]. We will conduct sensitivity analyses to determine the robustness of change in values of the main model parameters on ICER estimates.

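### The cost survey does not cover the study team's own cost of facilitation and partner engagement, yet the effect in the ICER comes from clinics that received both

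*Protocol article*

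**What the plan says.** Under Cost surveys, the article states the aim as "Measure cost to clinics of implementing the intervention" and names the informant: "Clinic managers will complete a survey once every year during the intervention providing personnel time, salary information, cost of materials". The start-up items are "1) personnel effort, software, hardware and costs related to workflow modification", then "2) time and effort assigning coordinator responsibilities and identifying eligible patients, (3) tele-mentoring delivery and participation". The execution items are "1) effort of staff assigned to care coordinator role, workflow modification(s), cancer documentation, EHR tool maintenance as applicable", plus healthcare use by survivors who receive the intervention. Facilitator time, the retreat, the mapping meetings and the convenings are not listed.

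Under Implementation strategies, the article says "Two strategies (partner engagement and practice facilitation) will support intervention". The study team supplies both. Partner engagement is a retreat of three sessions, about three months of meetings to map components onto workflows, and quarterly group meetings afterwards. Practice facilitation means "providing facilitation in quality improvement (QI) by a trained facilitator", and Intervention rollout adds monthly meetings set up by the facilitators.

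Randomization procedures assigns the time during and after the 12-month implementation to the treatment condition. Cost and cost-effectiveness analyses defines the ICER as "the incremental cost of the intervention compared to usual care divided by the incremental difference in the proportion of patients receiving guideline appropriate care". That section names no perspective and no further source of cost data.

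**The concern.** A cost-effectiveness ratio is interpretable only if its numerator and denominator describe the same package. Here the denominator is the gain in clinics that received three intervention components plus facilitation and partner engagement. The numerator, as far as the article describes it, rests on what clinic managers can report about their clinics' costs. A manager cannot be expected to know the study team's facilitator hours or what the retreat cost to run.

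The use of the result makes this matter. Cross-case synthesis promises an implementation guide for other health systems, and the Discussion sets out a care model meant for scale-up. A system that wants to reproduce the tested package would have to pay for facilitation and engagement from some budget. An ICER without those costs does not tell it what that would take.

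**Working it through.** **1. Does the supported time enter the effect estimate?** Inputs from Randomization procedures and Power calculation: 8 clinics, two crossing over every six months (four steps), 6 periods, 100 patients per clinic and period. Figure 2 is not shown, so I assume one common baseline period.

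- Total: 100 × 8 × 6 = 4,800, as stated.
- Usual care: 2 × (1 + 2 + 3 + 4) × 100 = 2,000, as stated.
- Intervention: 4,800 − 2,000 = 2,800, as stated.
- Of these, the first 12 months after crossover are 8 clinics × 2 periods × 100 = 1,600, or 1,600 / 2,800 = 57%.

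The plan's split reproduces only when every period after crossover counts as intervention. That agrees with Randomization procedures, although Power calculation describes the counts as leaving the implementation period out. If those periods were left out, 2,800 − 1,600 = 1,200 observations would remain, all from clinics that had already received the support. Either way, the effect includes facilitation and engagement.

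**2. Does the cost list include the support?** Set against the Cost surveys list:

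| Activity | Study-team cost listed? | Clinic staff time listed? |
|---|---|---|
| Tele-mentoring | Delivery is listed; whose cost is not said | Yes (participation) |
| Practice facilitation | No | Possibly, under personnel effort or workflow modification |
| Retreat | No | Possibly, under personnel effort |
| Mapping meetings | No | Possibly, under workflow modification |
| Quarterly convenings | No | Possibly, under personnel effort |

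**3. Effect of the omission on the ICER.** If a cost C per clinic is left out, n survivors are seen per clinic over the time considered, and the gain in proportion is ΔE, the ICER falls by

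C / (n × ΔE).

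This is positive whenever C and ΔE are positive. The inputs are ΔE = 0.15 (Power calculation) and n = 106 to 1,008 survivors per clinic and year (Setting, Table 1: smallest and largest). C = 10,000 USD is an assumption, because the documents give no cost figure. The result scales in proportion to C.

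Over one year:

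- n = 106: 10,000 / (106 × 0.15) = 10,000 / 15.9 = 629 USD per additional survivor screened.
- n = 1,008: 10,000 / (1,008 × 0.15) = 10,000 / 151.2 = 66 USD.

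Treatment time extends beyond one year. The 2,800 planned observations at 100 per clinic and period are 28 clinic-periods; 28 / 8 = 3.5 periods, or 1.75 years per clinic on average. If the gain is constant over that time:

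- n = 106: 629 / 1.75 = 359 USD.
- n = 1,008: 66.1 / 1.75 = 38 USD.

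**4. The same in relative terms.** If the omitted items were 10%, 25% or 50% of the full incremental cost (again assumed), the reported ICER would be 90%, 75% or 50% of the full-package value.

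**The case against.** The strongest reply is that a journal article condenses the plan. Cost surveys describes one instrument, and nothing says it is the only input to the ICER. Study-team costs could be recorded elsewhere, and their absence from a manager survey is to be expected. Part of this stands: the article does not say that these costs are valued at zero. But it does more than stay silent. It fixes a scope, an informant and an item list that together cannot yield study-team costs, and the ICER section adds no other source.

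A second reply is that the costing follows the article's own definitions: the intervention is training, tracking and coordinating, while facilitation and engagement are strategies that support it. A clinic perspective is a legitimate choice, but none is declared. Nor is the list clearly confined to one, since tele-mentoring delivery and survivors' healthcare use may reach beyond a clinic's own budget. The wording does not settle either item, so I would not call this a proven inconsistency. A declared clinic perspective would still leave the effect dependent on support that is not costed.

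A reader might also infer three stronger points, which the documents do not support:

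- That facilitation and engagement are wholly uncosted. Clinic staff time in them may fall under listed items.
- That the published ICER will be too favourable overall. The survey runs only during the intervention and collects healthcare use only for survivors receiving it. If usual-care costs are not netted out, incremental cost would be overstated and the ICER pushed the other way.
- That comparisons between clinics by size will be distorted. The article plans one ICER and no such comparison.

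The planned sensitivity analyses do not close the gap, because they vary the values of model inputs and a cost that was never collected is not one of them.

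**Conclusion.** The point holds in a limited form. As described, the ICER would set the effect of the full package against costs that omit the study team's share of facilitation, retreat, mapping and convenings. With a positive effect, this omission alone makes the ratio look more favourable; the net direction of all cost gaps remains open.

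The amount cannot be derived from the documents. The illustrative range of 38 to 629 USD per additional survivor screened, for each 10,000 USD omitted per clinic, rests on an assumed cost, the planned 0.15 gain and the Table 1 volumes. Its lower end also assumes a constant gain over 1.75 years.

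The primary effectiveness analysis is not affected. The issue deserves action because the economic result is meant for adopters and study-team time is hard to reconstruct afterwards.

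**What to change.** 1. Log study-team hours and expenses by clinic as they occur, for facilitation, the retreat, the mapping meetings, the quarterly convenings and the tele-mentoring faculty. Name this log as a cost source under Cost surveys.
2. State the perspective of the ICER under Cost and cost-effectiveness analyses.
3. Report the ICER twice: with the implementation-strategy costs (full package) and without them (clinic-only, labelled as such). This avoids a dispute over which perspective is right.

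The cost is a short time log for staff who already deliver these activities and a sentence or two in each section. The trial design and data collection from patients do not change. The full-package ICER will be less favourable than the clinic-only one.

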### Qualitative data collection

To guide qualitative data collection, we will use the Rapid Assessment Procedure Informed Clinical Ethnography (RAPICE), a method that uses trained qualitative fieldworkers for participant observation and interviewing [110]. We will use RAPICE to guide our collection of observational and qualitative data before, during, and after implementation.

#### Observations

We will also conduct direct observations of tele-mentoring sessions and clinic activities using a previously established observation template [111]. Observations will focus on clinic locations (e.g., waiting room, nursing area), circumstances (e.g., walk-ins, late arrivals), and visit type (e.g., new patient, annual, follow-up, survivorship care) to gain insight on how survivorship care is delivered. Facilitators will take short notes, later expanding them into full fieldnotes supplemented by existing documents such as flow sheets, schedules, protocols, and annual reports.

#### Clinic member interviews

We will contact clinics to set up site-visit logistics and to obtain up-to-date lists of clinic members. We will conduct in-depth, one-hour interviews with administrators and clinicians, care coordinators, and board members to elicit narratives about intervention experiences, feasibility, and sustainability. For example, clinician interviews will assess how survivorship care training and facilitated tracking and coordinating supports ongoing care management of survivors.

#### Patient interviews

We will conduct patient interviews to elucidate experiences of care coordination and PCM domains: attitudes toward follow-up care; competing demands; and comprehension of clinic communications [40]. We will purposively sample patients to compare between clinics. Patient Surveys will measure the *Picker Patient Experience of Care care coordination subscale* and other potential confounders and effect modifiers [112, 113]. We. Surveys will be administered by phone during the pre- and then again during the post-intervention period. We have already translated these survey measures in Spanish, made them culturally appropriate, and understandable by individuals with low literacy (*R01CA203856*)*.*

### Data analysis

Initially we will examine the distribution of each variable. We will then check for out-of-range values, outliers and abnormal values using graphical methods such as the box-plot. We will verify that the distributions of measures meet the assumptions of the statistical tests to be used, applying a formal test such as the Shapiro–Wilk’s test [114]. If the assumptions are not fulfilled, we will consider appropriate transformations or application of alternative methods such as non-parametric inference. Further, we will test whether baseline characteristics are well balanced between groups. If a baseline variable is not balanced, we will include it as a covariate in the analysis. To test the superiority of the intervention compared to the control (usual care) we will adopt the linear mixed-effect (LME) model for a cross-sectional stepped-wedge design. In this design it is assumed that the analysis will include data from subjects both before and after the crossover, with subjects distributed proportionately across the trial timeline. Our basic model is a mixed-effect regression model where the outcome of interest is the proportion of cancer survivors screened for other cancer types. The outcome will be transformed in the normal scale using a logistic transformation before fitting LME if needed. The model will include a cluster/clinic-specific random effect, fixed effects due to time/period, and an intervention indicator variable taking on the value “1” if the cluster is given the active intervention and “0” otherwise. As the assignment of cluster changes, so does the value of this indicator variable with time. Our primary aim is to test the significance of the intervention effect associated with the intervention indicator variable. The alternative model includes Heo et al. (2018), which argued that the time/period effect could be considered a random period-level model nested within the cluster level, resulting in a slightly different sample size [115]. For our primary outcome, we plan to use Hussey and Hughes’s (2007) model with the time/period effect as a fixed effect [34].

#### Power calculation

The primary outcome variable is continuous, for which Hussey and Hughes (2007) derived a closed-form analytical expression for power using linear mixed-effect model [34]. This formula is implemented in the PASS 2022 software, which is used for power calculation. From the historical records of recruitment feasibility, we propose to recruit 100 subjects (or more) per clinic in every six-month period. This results in a sample size N = 100*8*6 = 4800, out of which about 2000 will be under usual care and 2800 under intervention condition (excluding intervention implementation period in each clinic). We assume an ICC < 0.05 (within clinic association). We assume the difference in screening rate between intervention and usual care condition is ≥0.15 to guarantee ≥85% power, with a two-sided type-1 error of 0.05 (see power curve figure). Sample size using Heo et al. (2018) is slightly larger but still guarantees ≥ 80% power (checked using the swCRTdesign package in R software) [115]. A cross-sectional stepped wedge design assumes that outcomes are assessed for unique survivors every six months, and we recognize that eligible patients may return for regular clinic visits. However, for any eligible survivor, if the outcome of cancer screening in the past period is negative, then that past outcome does not affect the outcome of screening in the future period, and survivors who screened positive (in any period) are then not eligible for outcome assessment in future periods. The stepped-wedge design can be implemented in two forms: cross-sectional and repeated-measures. We have chosen a cross-sectional stepped-wedge design (open cohort), which assumes that clinics may evaluate new subjects during each observation window (i.e., every six months). While it is possible that a subject who screened negative in a previous period may return for screening in a later period (if still eligible), we expect the number of such repeat participants to be low. Importantly, for any given subject, a negative screening outcome in a previous period does not influence the likelihood of a positive outcome in a subsequent period. Subjects who screen positive in any period are referred for appropriate treatment and removed from future screening. Therefore, no sample size adjustment has been made for potential repeated observations within a clinic. Missing data is minimal in this cross-sectional design due to long-standing CHC relationships and ongoing partner engagement.

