### Randomization procedures

We will randomize 8 CHC clinics in blocks of two every six months in a stepped-wedge design (Fig. 2). Each clinic team will implement the intervention over a 12-month period. The time before the intervention will serve as the usual care (control) condition, while the period during and after the intervention will constitute the treatment condition.

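### The protocol both counts the 12-month implementation period as treatment and says the 2,000/2,800 split excludes it; the 85% power claim is safe only on the first rule

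*Protocol article*

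**What the plan says.** All references are to the protocol article.

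- **Randomization procedures** sets the wedge: "We will randomize 8 CHC clinics in blocks of two every six months in a stepped-wedge design". It adds "Each clinic team will implement the intervention over a 12-month period" and assigns that time to a condition: "the period during and after the intervention will constitute the treatment condition".
- **Power calculation** gives the cell size, "we propose to recruit 100 subjects (or more) per clinic in every six-month period", and the total, "This results in a sample size N = 100*8*6 = 4800". It then says that "about 2000 will be under usual care and 2800 under intervention condition (excluding intervention implementation period in each clinic").
- The power claim is "We assume the difference in screening rate between intervention and usual care condition is ≥0.15 to guarantee ≥85% power", two-sided at 0.05, with "We assume an ICC < 0.05 (within clinic association").
- **Data analysis** names the Hussey and Hughes model with fixed period effects and a random clinic effect. Its intervention indicator equals 1 once the clinic is given the active intervention, which fits the Randomization procedures rule. The hypotheses under **Outcomes** compare usual care with post-intervention periods, which fits exclusion better.

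The text does not state the number of calendar periods, the usual-care screening rate or the outcome variance. The design figure and the power curve are not shown in the copy reviewed.

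**The concern.** Two six-month periods per clinic, 16 clinic-periods in all if each clinic completes them within the calendar, are treated data under one section and absent under the other. This affects the estimand as well as the sample size. Counting implementation time averages the roll-out months into the effect; excluding it estimates the effect after roll-out. It also removes the data next to each crossover, which carry most of the within-period comparison in a stepped wedge.

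The stated counts do not settle which rule was used. On the direct reading of the sample-size product they are the counts of a wedge with nothing removed, although the parenthesis says that something was. A reader cannot tell which design the power figure belongs to, and the answer changes the power materially.

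**Working it through.** **Inputs from the protocol article.** 8 clinics, two per step, so 4 steps six months apart; 12 months of implementation = 2 periods per clinic; m = 100 per clinic-period; difference 0.15; two-sided alpha 0.05; ICC below 0.05.

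**Assumptions.** One baseline period before the first step. Usual-care rate p from 20 to 60%. Outcome variance s² is the average of p(1−p) and (p+0.15)(0.85−p), which simplifies to 0.06375 + 0.85p − p². Within-clinic variance is s²(1−ICC) and between-clinic variance is τ² = s²·ICC, with ICC 0.01 to 0.05. Normal approximation.

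**Step 1: the stated split.** Six calendar periods, nothing excluded:

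- Control periods by step: 1, 2, 3, 4. Two clinics each: 2 × 10 = 20 clinic-periods = 2,000.
- Treated periods by step: 5, 4, 3, 2. Two clinics each: 2 × 14 = 28 clinic-periods = 2,800.
- Total 4,800, exactly as stated.

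**Step 2: exclude 12 months from the same six periods.**

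- Treated periods by step: 3, 2, 1, 0. Two clinics each: 2 × 6 = 12 clinic-periods = 1,200.
- Total 2,000 + 1,200 = 3,200. The last two clinics give no treated data, and only period 4 contains both conditions.

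**Step 3: other calendars.** Eight periods with two dropped per clinic leave control periods 1, 2, 3, 4 and treated periods 5, 4, 3, 2. That is again 2,000/2,800 with six analysed periods per clinic, and only period 4 contains both conditions. Seven periods with one dropped also gives 2,000/2,800, but removes six months rather than 12.

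**Step 4: power.** For the complete design, with σ² the variance of a clinic-period mean, I clinics and T periods:

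Var = Iσ²(σ² + Tτ²) / [(IU − W)σ² + (U² + ITU − TW − IV)τ²]

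Here I = 8, T = 6, U = 28, W = 184 and V = 108, so IU − W = 40 and U² + ITU − TW − IV = 784 + 1,344 − 1,104 − 864 = 160. At s² = 0.25 and ICC 0.05, σ² = 0.2375/100 = 0.002375 and τ² = 0.0125:

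Var = 8 × 0.002375 × 0.077375 / (0.095 + 2.0) = 0.000702, so SE = 0.0265.

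Power = Φ(0.15/0.0265 − 1.96), above 0.999. The detectable difference at 85% power is (1.960 + 1.036) × 0.0265 = 0.079.

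For the incomplete designs the same model was fitted by generalised least squares with the excluded clinic-periods removed. At s² = 0.25 and ICC 0.05, six periods with two dropped gives SE 0.0584 and power Φ(0.15/0.0584 − 1.96) = 0.73. Eight periods with two dropped gives SE 0.0541 and power 0.79.

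Power at ICC 0.05 by assumed usual-care rate:

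| Design | 20% | 30% | 40% | 50% | 60% |
|---|---|---|---|---|---|
| Six periods, none excluded | 1.00 | 1.00 | 1.00 | 1.00 | 1.00 |
| Six periods, two dropped per clinic | 0.83 | 0.77 | 0.74 | 0.75 | 0.79 |
| Eight periods, two dropped per clinic | 0.88 | 0.83 | 0.80 | 0.81 | 0.85 |

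Over ICC 0.01 to 0.05 the second row spans 0.74 to 0.85 (0.73 at s² = 0.25) and the third about 0.80 to 0.88. With nothing excluded, the detectable difference at 85% power is 0.07 to 0.08.

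**Step 5: where 85% is reached.** At ICC 0.05 the break-even s² is 0.184 for six periods with two dropped and 0.214 for eight. Solving 0.06375 + 0.85p − p² for these values, power is below 85% for usual-care rates of about 18 to 67% and about 25 to 60% respectively.

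**The case against.** The strongest reply is that the counts may be right as printed. The 6 in the product could mean analysed periods per clinic. An eight-period calendar with two implementation periods dropped then reproduces 4,800, 2,000 and 2,800, parenthesis included. This stands. A reader might infer that the split proves nothing was excluded, but the text does not support that, because the calendar is in a figure that is not shown.

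Second, a reader might infer that the trial lacks its stated power. The documents do not show this either. Both the difference and the power are stated as lower bounds, and with nothing excluded power is about 1.00, so the claim is met; a conservative target difference is no error. Even under 2,000/1,200, power at ICC 0.05 is 0.93 at a 10% usual-care rate and 0.88 at 70%. A smaller ICC or larger cells also help: at 150 per cell, with s² = 0.25 and ICC 0.05, six periods with two dropped gives 0.88.

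Neither reply removes the contradiction. Under the eight-period reading the Randomization procedures section still counts as treatment the time that the Power calculation section leaves out, and power is still 0.80 to 0.83 for usual-care rates of 30 to 50%, below the level described as guaranteed.

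**Conclusion.** The contradiction is established from the text alone and concerns which data enter the primary analysis. Its effect on power is conditional:

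- Implementation counted as treatment, six periods: 2,000/2,800, power about 1.00. The 85% claim is safe.
- Twelve months excluded from six periods: 2,000/1,200 (N = 3,200), power about 0.73 to 0.85.
- Twelve months excluded from eight periods: 2,000/2,800, power about 0.80 to 0.88.

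So the claim is safe only if implementation time counts as treatment. If 12 months are excluded, it fails for mid-range usual-care rates and may hold outside them. These figures rest on one baseline period, 100 per clinic-period, ICC 0.01 to 0.05, an assumed usual-care rate of 20 to 60% and the Hussey-Hughes model. The power figure can be confirmed only as a lower bound for the complete design, because its variance input is not stated.

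**What to change.** State one rule for implementation time in both Randomization procedures and Power calculation, and make the intervention indicator in Data analysis follow it. State the number of calendar periods and the outcome variance or usual-care rate behind the power figure.

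- If implementation counts as treatment: delete the parenthesis and keep 2,000/2,800. The detectable difference at 85% power, about 0.07 to 0.08 under the assumptions here, can then be reported beside the 0.15 target.
- If implementation is excluded: give the counts for the actual calendar (2,000/1,200 if it has six periods, 2,000/2,800 if eight). Restate power from a re-run on that incomplete design, and change the Randomization procedures sentence.

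The cost is rewording and, if implementation is excluded, one re-run of the power calculation. No patients are added by the correction itself, though under exclusion the stated power may become less favourable.

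### The protocol both counts and excludes the 12-month implementation period, and under exclusion the claim of at least 80% power with a random clinic-by-period effect is not supported

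*Protocol article*

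**What the plan says.** The Randomization procedures section of the protocol article states "We will randomize 8 CHC clinics in blocks of two every six months in a stepped-wedge design" and "Each clinic team will implement the intervention over a 12-month period". On the status of those 12 months it says that "the period during and after the intervention will constitute the treatment condition".

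The Power calculation section assumes 100 patients per clinic per six-month period. It continues "This results in a sample size N = 100*8*6 = 4800", splits this into about 2000 usual-care and 2800 intervention patients, and adds that the split is made "excluding intervention implementation period in each clinic". It assumes an ICC below 0.05, a difference of at least 0.15 and a two-sided 5% test, and states at least 85% power under the Hussey and Hughes model with fixed period effects. For the alternative model, with a random period effect nested in clinic, it says that the sample size "is slightly larger but still guarantees" at least 80% power.

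The text gives no baseline screening rate, outcome variance or between-period correlation.

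**The concern.** The two sections assign the implementation months differently: one treats them as intervention time, the other leaves them out of the patient counts. In a stepped wedge this is more than bookkeeping. The periods just after crossover are where treated and untreated clinics are observed side by side, so dropping them removes much of the information about the effect that is free of calendar time.

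The sentence on the nested model is the article's only assurance that power survives period-to-period variation specific to a clinic. If it was computed with the implementation cells in, while the analysis leaves them out, a null result could be read as coming from a well-powered trial when it did not.

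**Working it through.** **Inputs from the document.** 8 clinics, 2 per step, 4 steps six months apart; implementation 12 months, i.e. two periods; 100 patients per clinic-period; difference 0.15; ICC 0.05 (the stated bound); two-sided alpha 0.05.

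**Assumed, because not given.** One common usual-care period before the first step; outcome variance v = p(1-p); between-period correlation r, i.e. the share of the ICC that persists across periods.

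**Step 1: which layout gives 2000/2800?** At 100 per cell this is 20 control and 28 treated cells. Clinics at step k (k = 1 to 4) have k control periods, so control cells = 2 x (1+2+3+4) = 20 in every layout. Treated cells:

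- Six periods, nothing excluded: 2 x (5+4+3+2) = 28. Fits the counts; contradicts the exclusion remark.
- Six periods, two excluded: 2 x (3+2+1+0) = 12. Does not fit.
- Eight periods, two excluded: 2 x (5+4+3+2) = 28. Fits the counts, the remark and the 12 months.
- Seven periods, one excluded: 2 x (5+4+3+2) = 28. Fits the counts, but excludes only six of the 12 months.

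With eight periods and two excluded, only period 4 holds clinics in both conditions (step 1 treated, step 4 control). In periods 1-3 only control clinics contribute, and in periods 5-8 only treated ones.

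**Step 2: power formula.** Generalised least squares with fixed period effects. Each clinic's vector of period means has covariance

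V = v[(1 - ICC)/100 + ICC(1 - r)] I + v x ICC x r J,

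where I is the identity matrix and J the matrix of ones. Setting r = 1 gives the Hussey and Hughes model; r < 1 adds the nested period effect. SE is the square root of the treatment-effect entry of (sum of X'V⁻¹X over clinics)⁻¹, and power = Φ(0.15/SE - 1.96).

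**Step 3: the plan's own 85%, eight periods with exclusion (r = 1).**

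- v = 0.25 (rate 50%): SE 0.0541, power 79%.
- v = 0.214 (mean of 0.25 x 0.75 and 0.40 x 0.60): SE 0.0500, Φ(3.00 - 1.96) = 85%.
- v = 0.21 (0.30 x 0.70): SE 0.0496, power 86%.

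So the stated 85% is reproduced at v of about 0.214.

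**Step 4: nested model, same layout, v held at 0.214.**

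| r | SE | power |
|---|---|---|
| 0.95 | 0.0562 | 76% |
| 0.90 | 0.0617 | 68% |
| 0.80 | 0.0713 | 56% |

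Power of 80% needs r of about 0.97 or more.

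**Step 5: sensitivity, same layout.**

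- v = 0.16 (0.20 x 0.80), ICC 0.05: 80% at r = 0.9 and 68% at r = 0.8.
- v = 0.21, ICC 0.02: 78% at r = 0.9 and 72% at r = 0.8.
- v = 0.21, ICC 0.01: 82% at r = 0.9 and 71% at r = 0.5.
- v = 0.25, ICC 0.05: below 80% at every r, since r = 1 gives only 79%.

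**Step 6: six periods, all cells counted, v = 0.25, ICC 0.05.** Fixed-period model above 99.9%; nested model 87% at r = 0.5, 98% at 0.8 and 99.6% at 0.9.

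**The case against.** The strongest reply is that the text writes the total as 100 x 8 x 6, which most plainly means eight clinics and six periods. That layout gives 20 and 28 cells with nothing dropped and agrees with the Randomization procedures section. Both power statements are lower bounds, and both hold there. Eight periods are stated nowhere in the text. All of this stands, and it rules out the inference that the two power claims cannot hold in any single layout. What it cannot do is save the exclusion remark, which would then be wrong.

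A reader might also infer that the trial's nested-model power is some definite low figure. The document does not support that: every value under exclusion rests on an assumed correlation and variance, 0.05 is the upper limit of the stated ICC, and 80% is reached in favourable corners. With seven periods and one excluded, nested power at v = 0.25 is 85% at r = 0.8 and 93% at r = 0.9, though that drops only half of the stated implementation time.

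Finally, the software inputs, the cited model's source and the power curve are not shown, and the Data analysis section can be read as replacing the fixed period effects by a random one. Power without fixed period effects would be about 99% or more. But that model would need a smaller sample, whereas the text says a slightly larger one, which fits fixed effects kept with variance added. The software check itself therefore cannot be called faulty; it cannot be matched to the layout that the text describes.

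The nested model is only the alternative, with the fixed-period model primary. That limits the consequence, but the primary model's own 85% depends on the same choice.

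**Conclusion.** The point holds as an internal contradiction on which the stated power depends. No reading leaves the text intact: six periods with all cells contradict the exclusion remark; six periods with 12 months excluded leave 12 treated cells, not 28; eight periods with exclusion match the counts but do not guarantee 80%.

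In the eight-period layout at ICC 0.05, calibrated to the plan's own 85%, a between-period correlation only slightly below 1 takes the nested model under 80%. That is the very variation the alternative model is meant to allow for. The size of the shortfall depends on the assumed correlation, variance and ICC. This does not show that the trial is underpowered: if implementation periods count as treated, both stated bounds are met comfortably for correlations of 0.5 or more.

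**What to change.** 1. Reconcile the Randomization procedures and Power calculation sections on whether implementation periods enter the primary analysis.
2. If they do, delete the exclusion remark and restate both powers for six periods with all cells counted.
3. If they do not, correct the period count, or else the 2000/2800 split, and replace the guarantee by nested-model power over a range of between-period correlations rather than at one chosen value.
4. In either case, give the number of periods, baseline rate, ICC and between-period correlation used, and quote both power figures for that single layout.

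The cost is a rerun of the power calculation and a few sentences. No clinics or patients are added, provided that the period count matches the data collection already planned. Under exclusion the published power may look less favourable.
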